##### Control arm: waitlist control

Child-parent dyads randomized to the control arm will continue treatment as usual. They will complete the baseline and immediate follow-up questionnaire at comparable times to families in the intervention arm; they will not complete the Extended Follow-up questionnaire. These dyads will be provided with the intervention at the next scheduled session after they have completed the immediate follow-up; the goal is to provide the intervention to controls as soon as possible to avoid differential attrition between the intervention and control arm. During the intervention sessions, participants in the control arm will complete all feasibility questionnaires before and after each session, pertaining to the intervention and their satisfaction with each session.

##### Explanation for the choice of comparators {6b}

Attention placebo control (APC) is preferable over treatment as usual or waitlist control for psychological interventions, to account for non-specific effects a group setting may offer such as social support/social attention [39]. However this design is rarely used in such trials [40]. Two key challenges may explain why the theoretical benefits of APCs have not been realized in practice and informed our decision to not use an APC in this current trial: (1) Disproportional drop-out has been documented; a study assessing a parent training program reported 18% and 50% attrition in the intervention and APC arms, respectively [40]. Furthermore, the reasons for drop-out were different; parents in the APC dropped out without reason or indicating a preference to be in the intervention rather than the APC arm, while parents in the intervention arm dropped out due to scheduling issues. (2) Potential for an ethical issue in a APC arm where participants’ comments and questions in discussions show a risky misunderstanding of key topics related to parenting, which should be addressed but where doing so is outside the protocol for the undirected discussion condition of the APC [40]. We view both these challenges as very likely to occur in the epilepsy population. Given that the aim of the current pilot trial is to evaluate feasibility, we will utilize a waitlist control arm and provide controls with the intervention as soon as possible, to avoid differential attrition between the intervention and control arm. For the subsequent full RCT, we are exploring possible programs to utilize as APC and are considering a cluster random allocation process where all the eligible participants recruited from each institution would be randomized as a group (cluster) to either the intervention or an APC arm where it is much easier to ensure blinding of participants to reduce the likelihood of uneven drop-out. Additionally, a specific a priori protocol could be developed for the APC to incorporate strategies for addressing misinformation about epilepsy.

#### Setting and delivery of the intervention

The program is delivered by non-clinician staff. We have partnered with our local community epilepsy agency, Epilepsy Southwestern Ontario (ESWO), whose staff will be provided the training required to deliver the intervention. Facilitators from ESWO will be trained on the M3 program by the team that created it, led by [name]. The training will be a 2-day online, interactive session following the standardized M3 training manual. Following the training, the ESWO facilitators will co-lead the program with one established trainer. At the half point of each program, a half-day booster-training session will occur online so that the program facilitators can extend their knowledge of the program and any facilitation issues that arise can be addressed.

The intervention will be delivered online, and a total of four facilitators will deliver each M3 session (two facilitators for the parent group, and two for the child group). Two research assistants will also be present for each online session (one for the parent group, and one for the child group). The role of the research assistants will be to report on intervention fidelity (quality of implementation; described below, in section “Outcomes {12}”) and to assist with the research aspects of the sessions (e.g., facilitating the process of parents completing questionnaires online).

#### Criteria for discontinuing or modifying allocated interventions {11b}

Adverse events, if any, are expected to be minor. There are no planned intervention modifications and no planned circumstances whereby participants will be removed from the intervention by the trial investigators. Participants may withdraw from the study and intervention at any time.

#### Strategies to improve adherence to interventions {11c}

Attendance will be tracked each week; if a session is missed, the research coordinator will contact the parent inquiring about the circumstances and identify if the trial investigators can provide any assistance to avoid missing future sessions. Parents are encouraged to utilize M3 skills outside of the scheduled intervention sessions, by being provided with parent cards that have extension activities (based on the theme of that week) to practice. Adherence to practicing or using the skills outside of the scheduled intervention sessions will be tracked at the start of each session; parents complete a questionnaire inquiring about the utilization of M3 skills or what may have prevented the utilization of those skills (see the supplementary file).

#### Relevant concomitant care permitted or prohibited during the trial {11d}

Usual care for participants continues throughout the trial. There is nothing prohibited.

#### Provisions for post-trial care {30}

Participants randomized to the control arm will be provided with the intervention in the next scheduled session, after they have completed the study. Adverse events, if any, are expected to be minor. Standard care is provided through the Ontario Health Insurance Plan.

#### Outcomes {12}

Each outcome is described below. Feasibility outcomes (primary objective) will be evaluated throughout the course of the study. Efficacy outcomes (secondary objectives) will be evaluated 0–2 weeks before the intervention (Baseline) and 1 week after the intervention (Immediate Follow-up). Secondary outcomes for the intervention arm will also be evaluated 10 weeks after the end of the intervention (Extended Follow-up). The timeline of assessment is presented in Table 2 and section “Participant timeline {13}”.

##### Primary outcome: feasibility

The primary objective of the trial, to evaluate the feasibility of implementing the intervention, will be assessed by evaluating (a) study procedures, (b) participant feedback and adherence to M3, and (c) intervention fidelity, as described below.

Study procedures will be evaluated by tracking (a) the number of patients contacted, (b) participating rate, (c) reasons and/or barriers for non-participation (such as the proportion of families without an internet connection and/or a computer/mobile device), (d) attrition, (e) participant burden (e.g., time to complete questionnaires), and (f) quality of questionnaire data (e.g., the proportion of missing data).

Participant feedback and adherence to M3 will be evaluated using three measures developed for this study (see the supplementary file). The first measure, the Weekly Parent Questionnaire, is completed online by parents at the start and end of each session. At the start of the session it asks about the utilization of M3 skills outside of the scheduled intervention sessions over the past week and whether any adverse events were experienced by the parent or child. At the end of each session, it asks about skills taught in that session and suggestions for improvement. The second measure, Parent Pre-Post Assessment, is completed online by parents at the start and end of the M3 program and evaluates understanding and utilization of the skills taught by M3, as well as participants’ satisfaction with the online program. The third measure, Child Pre-Post Assessment, is completed by children with the help of a research assistant through a video call prior to the first group session and after the program is completed. The measure evaluates children’s understanding of topics discussed in the group, such as how our brain works when we are upset and what mindfulness is. These questions will be read to the children by the researcher and are rated on a 3-point scale as indicated by a smiling, neutral and frowning face.

Intervention fidelity will be evaluated through two measures developed for this study (see the supplementary file). The first measure, M3 Adherence Checklist, is completed online, at the end of each session by facilitators and evaluates whether each planned task/activity was completed, any modifications that were made, problems that arose, and the facilitator's satisfaction with the session and the online format. The measure was designed to evaluate and document how each intervention session ran and was received by participants from the facilitators’ perspective. The second measure, Quality of Implementation, is completed online, at the end of each session by the research assistants present at each session and evaluates the facilitators’ presentation of materials, their confidence, and effectiveness at presenting materials.

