QOLCE-55		X				X	X
PCGRC						X	X
BASC-3		X				X	X
BRIEF		X				X	X
SF-12		X				X	X
CESD-R		X				X	X
GAD-7		X				X	X
PSI-4-SF		X				X	X
Family APGAR		X				X	X
GASE		X				X	X
Demographics/clinical		X				X	X
Weekly Parent Questionnaire			X	X	X		
Parent Pre-Post Assessment			X		X		
Child Pre-Post Assessment			X^a^		X^a^		
M3 Adherence checklist			X	X	X		
Quality of Implementation			X	X	X		
QOLCE-16 (if participant withdraws)						X	X

*Abbreviations: BASC-3* Behavior Assessment System for Children Scale, 3rd edition, *BRIEF* Behavior Rating Inventory of Executive Function, *CESD-R* Center for Epidemiological Studies Depression, Revised scale, *Family APGAR* Family Adaptability, Partnership, Growth, Affection, and Resolve, *GAD-7* 7-Item Generalized Anxiety Disorder, *GASE* Global Assessment of the Severity of Epilepsy, *PCGRC* Patient-Centered Global Ratings of Change, *PSI-4-SF* Parenting Stress Index, 4th edition Short Form, *QOLCE* Quality of Life in Childhood Epilepsy Questionnaire, *SF-12v2* 12-item Short-Form Health Survey

^a^Will be completed a few days before and a few days after the first and last M3 session

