Once enough participants are ready to be randomized, those in the queue for randomization will receive an individualized link to the baseline questionnaire and electronic gift card via email 2 weeks before the first scheduled M3 session of the intervention arm. These participants will have 2 weeks to complete the questionnaire but will be asked to complete it within a week, to allow for a 1 week buffer. A member of the research team will also connect with the parent and child to attain assent of the child, complete the child Pre Assessment, and offer a short tutorial of how to use Zoom (the video conferencing application) if the parent is unfamiliar with this platform. Upon completion of the online baseline questionnaire by parents, the research coordinator will randomize participants via REDCap. Those randomized to the intervention (and controls who are in the queue for the intervention) will be provided with instructions on how access the online sessions. Those randomized to the control arm will be told that they will be placed in the next scheduled M3 sessions, after they complete the Immediate Follow-up questionnaire. Participants who were unable to complete the baseline questionnaire will be placed in the next scheduled group of participants to be randomized. After the M3 program is completed, the Research Coordinator will contact the family again to have the child complete the Post Assessment.

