### Data collection and management

#### Plans for assessment and collection of outcomes {18a}

All data and questionnaires are captured online using REDCap. If needed, participants may request mailed questionnaires, which would be subsequently entered into REDCap by a member of the research team. Feasibility outcomes are collected throughout the course of the study (e.g., recruitment, randomization, retention, and the assessment procedures) by the research team. After each intervention session, the research assistant and facilitators will complete questionnaires on REDCap designed to assess adherence and quality of implementation. Facilitators will be emailed individualized links to the questionnaire through REDCap, whereas research assistants will be able to enter data directly on REDCap. On the day of an intervention session, participants will be emailed an individualized link through REDCap with the questionnaire they must complete before or at the start of the session and at the end of the session; these questions pertain to the content of the M3 sessions and their experience with the intervention.

Similarly, with respect to efficacy outcomes (Baseline, Immediate Follow-up, and Extended Follow-up questionnaire), participants will be emailed (through REDCap) an individualized link to the questionnaire along with an individualized link to a $25 gift card.

Individualized links will also be emailed through REDCap to clinicians who would complete a short questionnaire pertaining to the patient’s clinical characteristics.

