#### Plans to promote participant retention and complete follow-up {18b}

If a session is missed, the research coordinator will contact the parent inquiring about the circumstances and identify if the trial investigators can provide any assistance to avoid missing future sessions. If randomized participants are not able to attend the M3 sessions, but would still be interested in completing the Immediate and/or Extended Follow-up questionnaires, they would be encouraged to do so. If participants withdraw, the reasons will be recorded and they will be presented with the option of completing the parent-reported QOLCE-16 [45, 46], an abbreviated version of the QOLCE-55, at the Immediate and/or Extended Follow-up, that is estimated to take less than 5 min to complete. This will be important to the intention-to-treat analysis in an attempt to follow all participants randomized into one of the two study arms.

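### Parents who withdraw from M3 have no stated route to the closing satisfaction form, so program-level satisfaction, part of the primary feasibility outcome, will mainly describe finishers

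*Protocol article*

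**What the plan says.** Under Primary outcome: feasibility, participant feedback and adherence is one of three components of the primary outcome. The Parent Pre-Post Assessment is the measure named for the overall view of the program: it "evaluates understanding and utilization of the skills taught by M3, as well as participants’ satisfaction with the online program". It "is completed online by parents at the start and end of the M3 program". Table 2 (in Objectives {7}) marks it at sessions 1 and 8 and at neither follow-up. The child's form has a footnote that moves it away from the session ("Will be completed a few days before and a few days after the first and last M3 session"), and Implementation {16c} adds that "the Research Coordinator will contact the family again to have the child complete the Post Assessment". The parent form carries no such footnote.

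Session forms go out by link: "On the day of an intervention session, participants will be emailed an individualized link through REDCap" (section {18a}).

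For families who stop, section {18b} has the reasons for withdrawal recorded and says that "they will be presented with the option of completing the parent-reported QOLCE-16". Dyads who cannot attend but remain willing are encouraged to complete the Immediate and Extended Follow-up questionnaires. Participant timeline {13} says that control dyads receive M3 after they have completed the study and fill in no follow-up questionnaires afterwards. Statistical methods {20a} pools both arms for the feedback measures and summarises them descriptively.

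**The concern.** The trial exists to prepare a larger multi-centre trial, and a main question is whether the online format works for families. Parents for whom it did not work are among the most informative on that question. The schedule asks for an overall rating only at a point that those who have left will not reach. Section {18b} makes an effort to follow withdrawals on quality of life, a secondary outcome, in the interest of intention-to-treat, but makes no matching provision for this part of the primary outcome.

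This is a matter of data collection. If the closing items are never put to parents who stop, no later analysis can recover their answers.

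**Working it through.** **Step 1: who can supply a program-level rating, by the protocol's own schedule**

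- Parent who attends session 8, either arm: Parent Pre-Post Assessment scheduled.
- Parent who misses session 8 without withdrawing: unclear. The link in {18a} is sent on the day of the session and is not expressly limited to attendees.
- Intervention-arm parent who withdraws: QOLCE-16 offered and reasons recorded; no closing form.
- Intervention-arm parent who does not attend M3 but completes follow-up: Table 2 does not place the form at either follow-up.
- Control parent who starts M3 later and stops: no later questionnaire of any kind, because the study follow-up is already over.

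**Step 2: the loss figure.** The protocol gives no expected rate of stopping M3. The nearest figure is the attrition allowance in Sample size {14}. It reproduces: 38 + 38 = 76, and 76 / (1 − 0.24) = 100. It is used below as a stand-in for the share of starters who stop before the end of M3. That is an assumption, since it was set for the trial's sample size and not for dropout from the program.

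**Step 3: effect on reported satisfaction.** Let d be the share of starters who stop, p_f the proportion satisfied among finishers, and p_s the proportion satisfied among stoppers. If all finishers answer and no stopper does:

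- satisfaction over all starters = (1 − d) × p_f + d × p_s
- reported minus true = p_f − [(1 − d) × p_f + d × p_s] = d × (p_f − p_s)

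The protocol gives neither p_f nor p_s. With d = 0.24 and an assumed p_f = 0.80:

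- p_s = 0: 0.76 × 0.80 = 60.8%; overstated by 0.24 × 0.80 = 19.2 points
- p_s = 0.40 (half as often): 0.608 + 0.24 × 0.40 = 70.4%; overstated by 9.6 points
- p_s = 0.80 (equal): 80%; no error
- p_s = 1: 0.608 + 0.24 = 84.8%; understated by 4.8 points

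**Step 4: other assumed inputs**, with the all-starter figure running from no stopper satisfied to every stopper satisfied:

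- d = 0.24, p_f = 0.70: 53.2% to 77.2%
- d = 0.24, p_f = 0.90: 68.4% to 92.4%
- d = 0.10, p_f = 0.80: 72% to 82%

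The size depends wholly on how satisfied the stoppers are, and so does the sign.

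**The case against.** The strongest reply is that stoppers are heard in other ways. The Weekly Parent Questionnaire is given at every session: "At the end of each session, it asks about skills taught in that session and suggestions for improvement". The waitlist section describes the session forms as "pertaining to the intervention and their satisfaction with each session", and Participant timeline {13} says that all participants complete the same session questionnaires. Reasons for withdrawal are recorded, each missed session prompts a call about the circumstances, and facilitators record how each session was received. Attrition and missing questionnaire data are themselves feasibility outcomes, so the gap would be partly visible.

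Most of this stands. A reader might infer that satisfaction is asked only at the last session, or that nothing but the QOLCE-16 is obtained from those who leave; the document supports neither. What remains is that session-level feedback and a reason for leaving are not an overall rating of the program over the same set of families. Nor does attrition clearly show how many ratings are missing, because control dyads have already completed the study when they start M3, and the article does not say whether stopping then counts as attrition.

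A second reply is that the direction of any bias is unknown. That also stands. The one cited study for which the protocol gives reasons for intervention-arm dropout (18%, in the choice of comparators {6b}) attributes it to scheduling, not dissatisfaction.

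A third is that end-of-program understanding is by nature a measure in those who reached the end. That is fair, and it is why the fix concentrates on satisfaction and feedback. A reader might also infer that pre and post forms will be compared across different sets of parents. The protocol specifies only descriptive summaries, and restricting change to parents with both forms is ordinary analysis detail.

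**Conclusion.** The point holds in a limited form. Parents who withdraw from M3 have no stated route to the closing Parent Assessment, and control dyads who stop have no later questionnaire, so the program-level satisfaction summary will mainly describe finishers. For parents who miss session 8 without withdrawing, the gap is possible but not certain.

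A reader might go further and conclude that reported satisfaction will be too favourable by a known amount. The document does not support that: it gives no satisfaction figure for either group. The range of 0 to 19 points rests on three assumptions: 24% stopping M3, 80% of finishers satisfied, and stoppers no more satisfied than finishers. No stated threshold or progression rule depends on the result, and the questionnaire items are in a supplementary file that was not available for this review. This is a worthwhile and inexpensive improvement to one component of the primary outcome; it does not threaten the trial.

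**What to change.** In Outcomes {12} and section {18b}, state that the closing satisfaction and feedback items of the Parent Assessment will be offered by individual REDCap link to every dyad, in either arm, that attended at least one M3 session, either at withdrawal or in the week after session 8. Report the number answering out of all starters, next to attrition and reasons for stopping. While editing, reconcile the two descriptions of the session questionnaires: the waitlist section says they cover satisfaction with each session, whereas the Outcomes section lists skills taught and suggestions for improvement.

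The cost is one more automated email and a sentence in each section. REDCap already sends individual links, and the coordinator already contacts families after the program for the child's form. The downside is a few minutes asked of parents who stopped, some of whom will not reply, so the gap will be reduced and made visible rather than closed.

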##### Children’s health-related quality of life

The parent-reported 55-item Quality of Life in Childhood Epilepsy Questionnaire (QOLCE-55) [41–43] will be used to evaluate the HRQOL of CWE. The QOLCE-55 generates a total HRQOL score and four subscale scores evaluating cognitive, emotional, social, and physical functioning. Scores range from 0 to 100, with higher scores indicative of better HRQOL. The primary interest will be the mean total HRQOL score at the Immediate Follow-up (week 9), adjusting for the total HRQOL score at Baseline (week 0).

Although the QOLCE is a widely used HRQOL scale, no study has calculated the minimum clinically important difference (MCID). Using the methods described by Wiebe et al. [44], we will ascertain meaningful change in HRQOL for the QOLCE-55 using the parent-reported Patient-Centered Global Ratings of Change (PCGRC). This information will allow us to calculate the MCID for the QOLCE-55, and thereby identify the proportion of patients who experience a clinically meaningful change following intervention. The PCGRC consists of 5 items and asks participants to indicate the amount of change experienced relative to baseline in five areas (questions) that correspond to the QOLCE subscales: overall HRQOL, cognitive function (e.g., memory and thinking), emotional well-being, social activities/well-being, and physical activities/well-being. Ratings range from − 7 (a very great deal worse) through 0 (no change) to + 7 (a very great deal better).

If participants withdraw from the study, they will be presented with the option of completing the parent-reported QOLCE-16 [45, 46], an abbreviated version of the QOLCE-55, at the regularly scheduled times (Immediate and/or Extended Follow-up). The QOLCE-16 is composed of 16 items and is a shortened version of the QOLCE-55 and is estimated to take less than 5 min to complete. This will be important to the intention-to-treat analysis in an attempt to follow all randomized participants.

